#### Pain

Symptoms of pain will be measured with the pain scale of the Dutch version of the Minimum Data Set of the Resident Assessment Instrument (MDS-RAI) [34] and with the Pain Assessment Checklist for Seniors (PACSLAC-D) [37]. The MDS contains two pain items: 'pain frequency' and 'pain intensity'. In the MDS, pain frequency is coded as no pain (0); less than daily pain (1); and daily pain (2) in the last 7 days. Pain intensity is categorized as no pain; mild pain (0); moderate pain (1); and severe pain (2, times when pain is horrible or excruciating) in the last 7 days. The product of intensity and severity in this study has to be ≥2 to be defined as clinically relevant pain.

The validity and precision of pain measurement with MDS items have been established against the Visual Analogue Scale in a study involving 95 US nursing home residents [34]. The definition of pain in the MDS is ''Pain refers to any type of physical pain or discomfort of the body. Pain may be localized to one area, or be more generalized. It may be acute or chronic, continuous or intermittent (comes and goes), or occur at rest with movement. The pain experience is very subjective; pain is whatever the resident says it is." Coding instructions are ''Code for the highest level of pain present in the last seven days" [54].

The PACSLAC-D is a brief and manageable version of the Pain Assessment Checklist for Seniors with Limited Ability to Communicate [35] in Dutch that was developed by Zwakhalen [37], with a three component solution including 24 items. This version had high levels of internal consistency for the complete scale (Cronbach's alpha range 0.82-0.86) and for all subscales (alpha range 0.72-0.82).

Both the pain scale of the MDS-RAI and the PACSLAC-D will be assessed by the contact nurse of a particular resident at baseline and after 3 and 6 months.

#### Video registrations

At baseline, 5 minute standardized video recordings of the included patients will be made during both morning care and mealtime. This will be repeated after three months.

Independent, blinded raters will score the video-recordings, by using the PACSLAC-D. These video-recordings will also be used to independently code another pain and discomfort scale, the Dutch version of the Discomfort Scale- dementia of Alzheimer Type (DS-DAT) [26,55]. The DS-DAT is an observational scale with 9 items, and measures symptoms regarding vocalizations, breathing, facial expression, and body movement. The reliability and validity of the Dutch version has been established as high [55-57]. In addition, the video-recordings will be analyzed using the Facial Action Coding System (FACS) [58].

### Secondary outcomes

Secondary outcomes include symptoms of depression, an indication of the quality of life and changes in prescriptions of medication.

#### Depressive symptoms

Depressive symptoms will be measured with the Cornell depression scale and the depression rating scale of the Minimum Data Set Depression Rating Scale (MDS-DRS).

The MDS-DRS is a seven-item scale, with all items scored as, 0 (indicator not exhibited), 1 (indicator of this type exhibited at least once in the last 30 days and up to 5 days a week) or 2 (indicator exhibited daily or almost daily) [59]. The scores range between 0 and 14. The mood-items in the MDS 2.0 have good inter-rater reliability [54,60,61]. (With a cut-off point of 3, it differentiates well between residents with few or many depressive symptoms. Compared to (DSM-IV) psychiatric criteria for depression it has a high sensitivity (91%), and a lower specificity (69%) [59].

The Cornell Scale is a well-known, mostly caregiver-rated scale that is particularly suited to differentiate between cognitive and mood symptoms, and is sensitive to treatment effects over a wide range of depression severity. The scale has nineteen items that are based on the week prior to the interview and which are rated as absent, mild or intermittent, and severe. Symptoms are clustered into five main categories: mood related signs, behavioural disturbance, physical signs, cyclic functions, and ideational disturbance. Published inter-rater reliability kappa is 0.67, internal consistency is reasonable (0.84), and it has been found to be valid, based on comparison with the Hamilton Depression Rating Scale and Research Diagnostic Criteria [38,39].

#### Quality of Life (QoL)

The quality of life will be measured with the *Qualidem*. The Qualidem is an easy to administer and sufficiently reliable and valid rating scale that provides a quality of life profile of persons with dementia in LTC settings. The Qualidem can be used for evaluation as well as for research and practice innovation. Twenty-one of 40 items are suitable for people with very severe dementia [40-42]. Each subscale of quality of life is scored. It is not possible to calculate a total score of the Qualidem. The individual item scores for each subscale are summed: the higher the score, the better the quality of life.

### Demographics, baseline and control variables

Sex, age and cultural background of residents will be derived as demographic variables from structured questionnaires filled in by nurses. A subscale of the Residents Assessment Inventory (RAI) will be used to obtain co-morbidity and will be filled in by the nursing home physicians. They will also determine the stage of dementia, measured with the Global Deterioration Scale [29,62] and the Cognitive Performance Scale (MDS-CPS).

The MDS-CPS is a seven-category index, ranging from cognitively intact to very severely impaired. The scale has shown excellent agreement with the Mini-Mental State Examination (MMSE) in the identification of cognitive impairment in research [63].

The Global Deterioration Scale (GDS) [29] consists of a seven-point scale (1-7) ranging from 'no global impairment' (1) to 'very severe global impairment' (7). Characteristics of the nursing homes (such as available disciplines, amount and nature of followed education by health care professionals, unit sizes) will be carefully registered and taken in to account when performing the analyses.

#### Medication

Changes in prescriptions of analgesics and psychotropic drugs (coded as defined daily dosage-DDD) will be derived from the daily logs of contact nurses and will also be derived from the analysis of pharmacists' electronic patient records for the total study period of 26 weeks.

#### Apolipoprotein Epsilon 4

The status of Apolipoprotein Epsilon 4 (Apo-E4) will be determined as a baseline variable and will be taken from two buccal mucosa swabs (Catch-All swabs of the firm BIOzymTC example). The Apo-E4 protein may play a role in the response to (pharmacological) treatments [64]. It is currently unclear whether the Apo-E4 protein has an effect on non-pharmacological treatments, such as comfort interventions. Determining the Apo-E4 is therefore very important in intervention studies like the present study.

### Process variables

The actual use of the STA OP!-protocol will be derived from the daily logs of contact nurses for the total study period of 26 weeks, and from group interviews with contact nurses and nursing home physicians in weeks 26. The researcher/research assistant making site-visits once a week, will check the thoroughness of the log completion by the contact nurse. After the research period the internal formed focus group will take over this task, in order to facilitate implementation.

#### Patient files

The use and nature of non-pharmacological comfort interventions, as well as the nature and number of physical restraints will be derived from daily logs by the contact nurses and by studying patient files for the total study period of 26 weeks.

### Statistical analyses

To assess effects of the intervention on outcome variables, we will perform multilevel analyses with statistical adjustments for differences in the relevant baseline scores and control variables according to the intention-to-treat principle. Where no confounding is to be expected, univariate analysis will be applied. Both an intention-to-treat analysis and per protocol analysis will be performed.

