## Methods

### Study design

The study is a cluster randomized controlled trial. The clusters, Dutch nursing homes, are randomly assigned to either the intervention condition (implementation of the STA OP!-protocol) or the control condition (general training without the step-wise approach). Measurements take place at baseline, after 3 months (at the end of the STA OP!-training period) and after 6 months.

The study is single blinded i.e. the researcher will know the condition, while the research assistants performing the measurements and the persons analysing and score the video registrations are blinded. They will also not be informed about the specific research questions and conditions.

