### Sample size and power analysis

One of the primary outcome measures in this study is the CMAI, a behavioural observation scale with 29 behavioural items. Each item may be scored between 1 and 7, depending on the frequency of existing symptoms. The range on the CMAI is 29-203. In Dutch nursing homes the median is 44 [44]; there is no normal distribution, but the distribution of the change is more or less normally distributed. The standard deviation of difference scores (difference of 4) is 13. The expected difference is however larger (at least 10 points). To detect a 15% difference between the intervention (STA OP!-protocol) and control condition with an α = .05 and β = .80, 56 residents will be required. However, in cluster randomization, a design effect should be taken into account; clustering of items (consistency of CMAI items [ICC] among residents in a unit is .10) and also the effect of large differences in sample sizes per cluster enhances the design effect [45].

In this study the design effect was estimated at 1.5; So, 1.5 × 56 = 84 residents (after 4 weeks) will be needed in total to detect a 15% difference with an α = .05 and β = .80. However, we expect a 50% dropout due to non-response and loss to follow-up, i.e. we will need 168 patients in total; 84 in the intervention- and 84 in the control group.

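### Expected confounding is the wrong criterion for choosing between the adjusted multilevel model and univariate analysis in a cluster-randomised trial; as worded, the rule permits analyses that ignore clustering and omit the baseline covariate

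*Protocol article*

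**What the plan says.** In the protocol article, Statistical analyses, the main approach is: "we will perform multilevel analyses with statistical adjustments for differences in the relevant baseline scores and control variables", by intention to treat. The next sentence gives the exception: "Where no confounding is to be expected, univariate analysis will be applied". The section does not define univariate, does not name the outcomes to which the exception applies, and does not say whether the cluster level stays in the model.

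Three other sections bear on this:

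- Study design: "The clusters, Dutch nursing homes, are randomly assigned to either the intervention condition". The Randomization section adds that the entity allocated may be an institution, a home or a unit, depending on whether professionals work across sites.
- Sample size and power analysis: "in cluster randomization, a design effect should be taken into account". It gives an ICC of .10 for the CMAI within a unit and a design effect of 1.5.
- Table 1: every nurse-rated primary and secondary scale is recorded at baseline as well as at 3 and 6 months.

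**The concern.** Two modelling decisions hang on a criterion that governs neither.

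The first is whether to model the clusters. That need comes from the allocation of homes or units and from the correlation between residents who share them. It remains when every covariate is perfectly balanced. An analysis that treats residents as independent has standard errors that are too small and p-values that are too low, however little confounding is expected.

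The second is whether to adjust for the baseline score. In a randomised trial the main benefit is precision, which depends on how strongly baseline predicts follow-up and not on expected confounding.

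At stake is the validity of tests and intervals for any outcome analysed without the cluster level, and lost precision for any outcome analysed without its baseline. Because no outcomes are named, the primary scales are not excluded from the exception.

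**Working it through.** **Inputs** (Sample size and power analysis, unless noted)

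- SD of CMAI difference scores 13; expected difference at least 10 points.
- α = .05, taken as two-sided. The printed β of .80 is taken as power.
- ICC .10, read as the intracluster correlation; design effect 1.5; dropout 50%.
- More than half of eighteen institutions take part (Recruitment), so at least 10. The number of randomised entities is not stated.

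**1. The plan's own figures.** The normal approximation gives n per arm = 2 × (1.96 + 0.8416)² × 13² / 10² = 26.5, rounded up to 27, or 54 in total. The t-test version gives 27.52, rounded up to 28 per arm, or 56 in total, which is the stated figure. Then 56 × 1.5 = 84, and 84 / (1 − 0.5) = 168. All three stated totals reproduce, so the trial is sized on the premise that clustering inflates the variance by 1.5.

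**2. Type I error if clustering is ignored.** The naive standard error is too small by a factor 1/√DE, where DE is the design effect. A nominal two-sided 5% test then rejects a true null with probability 2 × [1 − Φ(1.96 / √DE)].

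At DE = 1.5:

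- 1.96 / √1.5 = 1.600, so type I error = 0.1095, about 2.2 times nominal.
- A nominal 95% interval covers 1 − 0.1095 = about 89%.
- 1/√1.5 = 0.816, so the standard error is understated by about 18%.

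**3. Check by simulation.** With equal clusters, 1 + (m − 1) × 0.10 = 1.5 gives m = 6, and 84 / 6 = 14 clusters. Both figures are assumptions; the article states neither. In 20,000 simulated null trials with 7 clusters of 6 per arm and ICC .10, a t-test on residents rejected in 11.1% and a t-test on cluster means in 5.1%.

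**4. Range.** The 1.5 is given in the CMAI calculation only, so other design effects must be assumed:

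| Assumed design effect | Type I error, clustering ignored |
|---|---|
| 1.1 | 0.062 |
| 1.25 | 0.080 |
| 1.5 (plan, CMAI) | 0.110 |
| 2.0 | 0.166 |
| 2.58 | 0.222 |

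The last row corresponds to ICC .10 with all 168 residents analysed in 10 clusters: 168 / 10 = 16.8, and 1 + 15.8 × 0.10 = 2.58.

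**5. The other reading.** If univariate means a multilevel model with treatment as the only predictor, the cluster level remains and this source of inflation disappears. What is lost is precision. At resident level, adjusting for a baseline value whose correlation with follow-up is ρ multiplies the variance by about 1 − ρ². The article gives no ρ, so this loss cannot be quantified.

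**The case against.** The strongest reply is that univariate may mean only unadjusted. The first sentence of the section commits to multilevel analyses without condition. Confounding is the usual reason for adding or omitting covariates, and the sample size section shows that the authors know clustering must be allowed for. This stands as a fair reading. A reader might infer that the plan abandons the multilevel model and so doubles the false-positive rate, but the text does not say so. It only fails to rule it out.

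A reader might also infer that the choice of model will follow inspection of the data, or that adjustment depends on observed imbalance. The article supports neither. The exception looks forward to what is expected, and adjusting for differences in baseline scores is ordinary wording for using baseline as a covariate.

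On baseline, the sample size section works with change scores ("The standard deviation of difference scores (difference of 4) is 13"), and a univariate comparison of change would still use the baseline value. That is possible, but the exception does not say that change is the outcome, and a change score is not the same as adjustment for baseline.

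It is also true that the section on demographics, baseline and control variables promises to take nursing home characteristics into account. That makes it less likely that primary outcomes would be treated as free of confounding, but it does not exclude it.

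Finally, an article may leave the model specification to an analysis plan. That covers omissions. It does not cover an explicit rule with the wrong criterion.

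**Conclusion.** The point holds as a defect in the stated rule. Expected confounding should decide neither whether the cluster level is modelled nor whether the baseline value is included, and the wording permits an analysis at odds with the trial's own sample size reasoning.

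The size is conditional. The 11% figure requires that clustering is ignored and that the CMAI design effect of 1.5 applies. The 6% and 22% ends of the range rest on assumed design effects, since no ICC is given for the other outcomes and no number of clusters is stated. If the univariate analyses keep the cluster level, type I error stays near 5% and the remaining cost is precision. Since the two readings differ this much and the exception is not confined to minor outcomes, the sentence should be corrected before analysis.

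**What to change.** Replace the sentence on univariate analysis with a statement to this effect:

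> Every analysis of an intervention effect, adjusted or unadjusted, includes a random effect for the entity that was randomised (institution, home or unit, as allocated). The main analysis of each outcome measured at baseline adjusts for the baseline value of that outcome, regardless of expected confounding or of baseline differences between the arms.

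Unadjusted results can still be reported beside the main analysis, provided they keep the cluster level.

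The cost is one or two sentences in the protocol or analysis plan. The baseline scores are already scheduled, and the Randomization section already assigns a number to each institution, home or unit, so no extra data or staff time is needed.

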### Ethical approval

The study has been approved by the Medical Ethics Review Committee of the VU University Medical Center Amsterdam (registration number 2009/119).

## Discussion

This study will evaluate the use and effectiveness of the Dutch version of the STI-protocol. The transfer from the American design to the Dutch design has necessitated several changes due to of the different organisation of healthcare systems. Next to the similarities between the original STI and the Dutch version, e.g. the stepwise approach and essentially the same content of each step, there are some differences. For instance, the presence of a nursing home physician and psychologist adds clinical expertise to the team. It will be interesting to see if these differences will influence the effects of the intervention. This expertise is also available in the control setting. This might therefore lead to smaller differences between control and intervention then in the USA, but it might also prove to strengthen the stepwise approach, and show stronger effects. Furthermore, the question arises whether the addition of a standard observational pain scale contributes to pain assessment.

In our design are also some essential differences with the RCT Kovach undertook. We decided to use the CMAI and NPI-NH as behavioural outcome measures, and PACSLAC-D and MDS-RAI pain scale as pain measures. In the STI-study, the DS-DAT was used, which is essentially a discomfort scale. By adding measures for depression (MDS depression rating scale and Cornell) and quality of life (Qualidem) we believe we have the opportunity to study more precisely the effects of this stepwise protocol. To tackle the problem of using observational scales, which are best filled out by staff who know the patient well, yet who might be biased because of the intervention, we have added video recordings that will be scored by independent raters. We will also meticulously register the medication used, and interventions that are performed. By taking Buccal mucosa swabs, we will be able to study if there are responder differences caused by the Apo-E4 status.

A difficulty in research in nursing home care is that the usual care of the control groups is not standardized. Although nurses and nursing home physicians will have some routines and standard procedures in caring for residents with pain or affective discomfort, standard care will differ between nursing homes. Therefore, it is important that during the total assessment period all prescriptions of analgesics and psychotropic drugs, and non-pharmacological comfort interventions are carefully registered. Another difficulty in this study is the variability in the amount of training between the control and intervention condition. In the control condition the team receives a standardized training program focused on challenging behaviour and pain, which explicitly does not contain a stepwise approach. The intervention training is specifically designed to work with the stepwise STA OP!-method, and this stepwise approach results in extra training sessions. A confounder may therefore be the extra amount of attention in the intervention group, with a possible stronger Hawthorn effect.

In conclusion, pain and challenging behaviour are a major problem in moderate to severe dementia patients in nursing homes. This study aims to contribute to the evidence-based treatment of nursing home residents who experience discomfort, pain and behavioural symptoms.
